### 3.2. Exclusion Criteria

Patients who meet any of the following conditions are not eligible.

- 1) Patients who are HBs, HCV, HIV or HTLV-1 antibody-positive or HBs antibody-negative but have HBV-DNA detected by HBV-DNA quantitative testing.
- 2) Patients who have been taking or injecting corticosteroids (methylprednisolone 10 mg/day or higher or equivalent) or immunosuppressive drugs within at least 2 weeks prior to the start of the study product.
- 3) Women who are pregnant, lactating, or planning to become pregnant during the study and men who do not agree with using any of effective contraceptive methods under the guidance of a physician during the study period or up to 14 days after the last dose of the study product.
- 4) Patients with active autoimmune disease requiring systemic or immunosuppressive therapy with corticosteroids or biologic agents.
- 5) Patients who have experienced immune-related adverse events with immune checkpoint inhibitors.
- 6) Patients with poorly controlled diabetes mellitus.
- 7) Patients with severe lung disease (mMRC Breathlessness Scale Grade 2 or higher) or with a history of non-infectious interstitial lung disease requiring steroid treatment.
- 8) Patients with significant cardiac disease (NYHA class III or greater).
- 9) Patients with concurrent multiple cancers.
- 10) Patients who are unable to use contrast agents in radiograph (e.g., allergy, kidney disfunction).
- 11) Patients with a history of hypersensitivity to human serum albumin products or proteins of foreign origin.
- 12) Patients who, at the time of informed consent, are participating in other clinical trials or clinical studies and are receiving other investigational products or are judged by the PI or SI to have residual effects of adverse events

 If HCV antibody is positive, HCV-RNA quantification test is performed and negative result is acceptable for inclusion.

 Women of childbearing potential include all women who have experienced menarche, have not undergone sterilization procedures (hysterectomy, bilateral tubal ligation or bilateral oophorectomy, etc.), and have not reached menopause. Menopause is defined as no menstruation for at least 12 consecutive months without any other medical reason.

caused by such products.

- 13) Patients with completely identical genotypes of HLA-A, B and C to the investigational product.

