#### 5.4.2. Subjects

- 1) After obtaining written consent, a screening test will be performed.
- 2) The PI or SI will confirm that subjects meet the selection criteria and do not violate the exclusion criteria regarding the screening test results.
- 3) The PI or SI will consult with at least two physicians comprising the study coordinating committee regarding the appropriateness of the judgment regarding eligibility. If the subject is finally judged "eligible," the PI, SI, or study coordinator will enroll the subject in the study.
- 4) The PI, SI, or study coordinator fills in the information necessary for subject registration and faxes it to the Chiba University Hospital Data Center. The PI or SI will confirm the eligibility and start the study treatment once the subject is determined to be eligible. Once a subject has been registered, the registration will not be cancelled. In the event that an error or duplicate registration is discovered, the Chiba University Hospital Data Center will be notified immediately.

In the event that the first dose cannot be administered within the specified period due to factors other than the subject's medical problems including fever caused by temporary infection (e.g., influenza infection), or the quality of DC/Gal or iPS-NKT cells (e.g., the cell count of DC/Gal or iPS-NKT cells was less than the expected dose). In such cases, the subject may be re-registered according to the procedures described in 3) and 4) above after conducting

the necessary screening tests again.

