## 5.9. Criteria of treatment and study discontinuation for each subject

### 5.9.1. treatment discontinuation

If any of the following criteria are met, the PI or SI will discontinue administration of DC/Gal or iPS-NKT cell. If administration is discontinued, the subject will be shifted to the observation period from the date when the decision to discontinue administration was made, and testing and assessment will be continued in accordance with the study schedule.

- 1) DLT occurs after administration of DC/Gal, or all adverse events of Grade 3 or higher that occurred during the study period do not recover or improve to Grade 1 or clinically manageable Grade 2 by the time immediately before administration of DC/Gal or iPS-NKT cell.
- 2) Subject develops an infectious disease requiring treatment that does not recover or improve to Grade 1, or does not improve to a clinically manageable Grade 2 by the time immediately prior to administration of DC/Gal or iPS-NKT cell.
- 3) SpO2 (room air) is maintained below 90%.
- 4) Grade 2 or higher on the mMRC shortness of breath scale (see Appendix 3) in the examination before administration of DC/Gal or iPS-NKT cells.
- 5) Requirement for the discontinuation from the subject.
- 6) Other cases in which the need to discontinue the administration of DC/Gal or iPS-NKT cell to the subject are recognized by the PI or SI.

The PI or SI should record the date of discontinuation, reason for discontinuation, and other necessary information.

In the case of discontinuation of DC/Gal or iPS-NKT cell administration, the "date of discontinuation" is not the date when the event causing the discontinuation occurred or became known, but the date when the PI or SI decided to discontinue.

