**Table 16 Study Calendar**

|                                           |   | Screening  | DC/Gal Prep. | Treatment Period |    |   |   |    |    | Observation Period  |                 |    | Termination |
|-------------------------------------------|---|------------|--------------|------------------|----|---|---|----|----|----------------------------------|-----------------|----|-------------|
| Day                                       |   | -42~
-8 | -7           | 1                | 6  | 7 | 8 | 13 | 19 | 1                                | 15              | 28 | —           |
| Allowance (days)                          |   |            |              | +3               | +3 | — | — |    | ±3 | ±3                               | ±7              | ±7 | +7          |
| Informed consent                          | ● |            |              |                  |    |   |   |    |    |                                  |                 |    |             |
| Demographics                              |   | ●          |              |                  |    |   |   |    |    |                                  |                 |    |             |
| Eligibility                               |   | ●          |              |                  |    |   |   |    |    |                                  |                 |    |             |
| Pregnancy test a)              |   | ●          |              |                  |    |   |   |    |    |                                  |                 | ●  | ●           |
| Infection test b)              |   | ●          |              |                  |    |   |   |    |    |                                  |                 |    |             |
| Chest X ray                               |   | ●          |              |                  |    |   |   | ●  |    | ●                                | ●               | ●  | ●           |
| ECG                                       |   | ●          |              |                  |    |   |   |    |    |                                  |                 |    |             |
| Enhanced CT or MRI                        |   | ●          |              |                  |    |   |   |    |    |                                  | ● h) |    | ●           |

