### 7.1.1. Screening test

After obtaining consent, the screening tests are initiated. The PI or SI will perform the following screening tests and enroll patients who meet the selection criteria and do not violate the exclusion criteria. The test items shall be as described below.

- Body weight (usu. one's own)
- Vital signs
- ECOG PS
- Hematological examination
- Blood biochemical tests (including HbA1c)
- Coagulation test
- Urinalysis
- Pregnancy test (for women of childbearing potential only)
- Infectious disease test (HBs antigen, HBs antibody, HBc antibody, HCV antibody, HIV antibody or HTLV-1 antibody)
- 12-lead ECG test
- Chest X-ray
- Contrast-enhanced CT scan (vascular and tumor evaluation)
- HLA testing (up to area 2 by Luminex method)
- Anti-HLA antibody test

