#### 7.1.3.1. Cell preparation period (Day -7)

One week prior to DC/Gal administration, apheresis is performed after checking vital signs to create autologous DC/Gal.

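### The assessment calendar checks two of the protocol's exclusions poorly: mMRC is first scheduled after apheresis, and the only pregnancy test before dosing can be 42 days old at first product

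*Protocol*

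**What the plan says.** **mMRC.** Protocol Section 3.2, exclusion 7, bars "Patients with severe lung disease (mMRC Breathlessness Scale Grade 2 or higher". Section 5.4.2 has the investigator confirm the criteria against the screening results, and Section 5.1 registers subjects on those results. Section 7.1.1 introduces its list with "The test items shall be as described below"; mMRC is not on it. Nor is it in the subject information of Section 7.1.2 or in the screening column of Table 16. Table 16 and Section 7.1.3.2 place it on Days 1 and 6, before each product.

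Between screening and Day 1, Section 5.4.2 says "Once a subject has been registered, the registration will not be cancelled", and Section 7.1.3.1 says "One week prior to DC/Gal administration, apheresis is performed after checking vital signs to create autologous DC/Gal". Section 1.2.2.10 describes a 7-day incubation. On Day 1, Section 5.7 requires that no discontinuation criterion is met, and Section 5.9.1(4) lists "Grade 2 or higher on the mMRC shortness of breath scale".

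**Pregnancy.** Exclusion 3 begins "Women who are pregnant". The "Pregnancy test" row of Table 16 is marked at screening (Day -42 to -8), on observation Day 28 and at termination. Sections 7.1.1 and 7.1.3.3 agree with it. The Day 1 and Day 6 lists in Section 7.1.3.2 contain no pregnancy test, and Section 5.9.1 has no specific pregnancy item. The rationale for exclusion 3 says that effects of iPS-NKT cells on the fetus have not been confirmed, and Section 1.2.4.4 says that reproductive toxicity studies will not be done.

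**The concern.** An exclusion defined by a score needs that score before the patient is committed. Here the commitment (registration, apheresis, manufacture of a patient-specific lot) comes first, and the first scheduled score comes at the bedside on the day of injection. A patient at mMRC Grade 2 could undergo apheresis for a product that the protocol's own Day 1 rule then forbids.

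The pregnancy gap is of another kind. Exclusion and schedule do not contradict each other, but the schedule lets both products be given on an old result. In a first-in-human combination with unconfirmed fetal effects, a pregnancy that began or became detectable after the screening test would not be found by any scheduled test before dosing.

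**Working it through.** No sample size, power or error rate is involved; the check is day arithmetic on Table 16.

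**Day numbering.** Section 7.1.3.1 puts apheresis on Day -7, one week before DC/Gal on Day 1. That fits a calendar without a Day 0: 1 - (-7) - 1 = 7 days. For a screening day s < 0 and a dosing day d > 0, the age of a result is d - s - 1. If a Day 0 exists, add 1 day to each age at a dose.

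**mMRC, in sequence:**
1. Screening tests, Day -42 to -8: no mMRC.
2. Registration on the screening results.
3. Apheresis on Day -7, after vital signs only.
4. DC/Gal culture, 7 days.
5. First scheduled mMRC on Day 1, 7 days after apheresis (8 with a Day 0).

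The threshold at step 5 is the one in exclusion 7, so a patient with stable Grade 2 breathlessness meets the stopping criterion on the first day it is looked for.

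**Age of the pregnancy result:**

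| Product | Test on Day -8 | Test on Day -42 | Test on Day -42, doses delayed |
|---|---|---|---|
| DC/Gal, Day 1 | 1 + 8 - 1 = 8 days | 1 + 42 - 1 = 42 days | 42 + 3 = 45 days |
| iPS-NKT, Day 6 | 6 + 8 - 1 = 13 days | 6 + 42 - 1 = 47 days | 47 + 3 = 50 days; 47 + 3 + 3 = 53 if both slip |

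**Next scheduled test.** If observation Day 1 is 14 days after iPS-NKT (Section 5.1), observation Day 28 is study Day 6 + 14 + 27 = 47. That is 46 days after DC/Gal, before the ±7 day allowance.

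**Pre-dose checks.** Section 5.7 refers only to the discontinuation criteria. Section 5.9.1 could reach pregnancy only through its general investigator-judgement item, which prompts no test. The Day 1 list does recheck one entry condition, the month since previous treatment, so the protocol already accepts rechecking eligibility on that day.

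**The case against.** The strongest reply is that Section 7.1.1 is not the whole eligibility check. Section 3 admits only patients who meet no exclusion, Table 16 has an eligibility item at screening, Section 5.4.2 requires consultation with at least two coordinating-committee physicians, and Section 7.1.2 records history and complications. Other history-based exclusions, such as NYHA class or active autoimmune disease, are not listed as tests either. This stands in part: a careful investigator can grade mMRC during that review. But Section 7.1.1 says "The PI or SI will perform the following screening tests and enroll patients who meet the selection criteria", and mMRC has its own calendar row that is blank at screening. The protocol treats it as a scheduled assessment and schedules it late.

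On pregnancy, the schedule is internally consistent, exclusion 3 also bars women planning pregnancy, and Section 7.1.3.6 follows any pregnancy to its outcome. A woman who conceives after a negative screening test was not ineligible at registration. All of that is correct. But a bar on planned pregnancy does not cover an unplanned one, and outcome follow-up acts after exposure.

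Three stronger readings are tempting, and the documents do not support them:
- A reader might infer that patients at mMRC Grade 2 would be treated. Sections 5.7 and 5.9.1(4) stop administration first.
- A reader might infer that each such patient uses up a place in a dose cohort. Section 10.1.1 limits the safety population, and so the DLT population drawn from it, to subjects treated with auto-DC/Gal. Sections 5.2 and 10.1.1 replace non-evaluable subjects. Irrevocable registration does not consume a DLT place.
- A reader might infer that, without a screening score, new deterioration cannot be told from long-standing breathlessness. SpO2, ECOG PS, chest X-ray and history are all collected at screening, and no rule requires a baseline mMRC for comparison.

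**Conclusion.** The point holds as a scheduling weakness with a patient-safety consequence; it does not touch the primary analysis. For mMRC, each affected patient could bear one avoidable apheresis, with one autologous lot wasted and at least the manufacturing week lost. This depends on the eligibility review not having graded mMRC informally. The documents give no basis for estimating how often that would happen.

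For pregnancy, the result is 8 to 42 days old at DC/Gal (up to 45 with the allowance) and 13 to 47 days old at iPS-NKT (up to 53 if both doses slip), assuming no Day 0. Few participants may be of childbearing potential, but the lower age limit is 20 and the protocol provides for this group. This part is a gap in coverage, not a contradiction and not a case of ineligible patients being registered.

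**What to change.** Reconcile the schedule with the protocol's own exclusions:
- Add mMRC to the Section 7.1.1 list and to the screening column of Table 16, to be recorded before registration. Keep the Day 1 and Day 6 assessments.
- For women of childbearing potential, add the urine qualitative pregnancy test already used in the study (Table 16, note a) to the Day 1 list in Section 7.1.3.2 and to Table 16, with the result known before DC/Gal. Urinalysis is already done at that point.

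The cost is one bedside question at screening and one urine strip on Day 1, plus the amendment wording. No dose, threshold, endpoint or analysis population changes.

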#### 【Rationale】

- 1) When iPS-NKT cells are administered intravenously, they have been found to accumulate in the liver. In this study, iPS-NKT cells were administered intravenously into tumor-feeding arteries, and although it is expected that there will be little systemic circulation, the eventual effect on the liver cannot be ruled out, and therefore, this setting was determined based on consideration of the safety of the subjects.
- 2, 4-5) The iPS-NKT cells are intended for direct and indirect immune activation in the target patients and were set up to exclude the influence of diseases and drugs that affect the immune status of the target patients.
- 3) Since the effects of iPS-NKT cells on the fetus and fertility have not been confirmed to date, the dose was set to avoid such effects in the target population. Since iPS-NKT cells administered into the body are considered to be almost completely eliminated from the body on the seventh day after administration, a contraceptive period was established.
- 6-8) Considering the safety of the subjects.
- 9) This was established to exclude the impact of adverse events due to cancers other than head and neck. The time period was set based on the recurrence rate after curative treatment of gastrointestinal cancer, which is a particularly frequent overlapping cancer of the head and neck, and because the risk of recurrence is considered to be high within 2 years.
- 10) Since the use of contrast enhancements is mandatory in this study to confirm tumor-feeding arteries in the subject
- 11) Considering the subjects' safety
- 12) To exclude the effects by other experimental agent on other clinical trials.
- 13) Considering the PK/PD analysis, we need to detect the iPS-NKT cells with different genotype from subjects one.
- 14) Because it is impossible to conduct this study in patients who are unable to have component blood samples taken for DC/Gal preparation.
- 15) Other settings were made to allow for exclusions when the investigators judged that the study could not be safely conducted.

---

 The genotype of iPS-NKT cell used in this study is as follows:  
A\*26:01-B\*35:01-C\*03:03  
A\*26:03-B\*35:01-C\*03:03

## 4. Informed Consent

### 4.1. Preparation and Revision of Consent and Other Explanatory Documents

The PI shall prepare the consent document and other explanatory documents used to obtain consent for participation in the clinical trial from the subject, using plain language as much as possible. If it is deemed necessary to revise the consent document and other explanatory documents, these documents shall be revised.

The PI shall submit the prepared or revised consent document and other explanatory documents to the Clinical Trial Review Committee for its approval.

### 4.2. Timing and Method on Informed Consent

#### 1) Obtaining Consent

PI or SI should hand the informed consent form and related documents approved by IRB etc., and should carefully explain the contents described below in “4.3. Contents of Explanation for subjects” to the candidate patients. And CRCs can supplementally explain for them if needed. PI or SI should perform the Screening tests after confirming the subjects’ comprehension and obtaining the written, free and voluntary consent.

#### 2) Explanation

The PI or SI will provide the subject with an opportunity to ask questions and sufficient time to decide whether or not to participate in the study before obtaining consent, and will answer the subject's questions to the subject's satisfaction.

#### 3) Filling out a Consent Form and Delivery of the Explanation Document

When consenting, the PI or SI who provided the explanation should affix his/her name and seal or sign the consent form and fill out the date of the explanation. The subject shall affix his/her name and seal or sign the consent form and fill out the date of consent. If the study coordinator provided supplementary explanations, he/she should also affix his/her name and seal or sign the consent form and fill out the date of the explanation. After obtaining consent, a copy of the explanation document and the informed consent form should be given to the subject.

#### 4) Amendment of Informed Consent Form

Whenever the PI or SI revises the informed consent form or other explanatory documents due to the acquisition of new information that may be relevant to the subject's consent, the PI or SI will explain the revised informed consent form or other explanatory documents to the subject and obtain the subject's written, free and voluntary consent to continue participating in the study. The subject's consent for continued participation in the study shall be obtained in writing. If new important information is obtained that could affect the subject's consent, this information will be immediately provided to the subject, recorded in writing, and the subject's continued participation in the study will be confirmed. ■

#### 4.3. Contents of Explanation for subjects

The following items should be included in the explanatory document prepared by the PI:

- 1) The name of the regenerative medicine to be provided and the fact that a regenerative medicine provision plan has been submitted to the Minister of Health, Labour and Welfare.
- 2) The name of the medical institution providing the regenerative medicine, etc., and the names of the administrator, PI, and physician or dentist providing the regenerative medicine, etc. at the medical institution (In the case where regenerative medicine, etc. is conducted as a multi-center collaborative study, the name of the PI and the names of other medical institutions where the regenerative medicine, etc. is conducted and the name of the administrator of the medical institutions.)
- 3) Purpose and details of the regenerative medicine, etc. to be provided
- 4) Information on the cells to be used for regenerative medicine, etc.
- 5) Reason for selection as a recipient of regenerative medicine, etc. (limited to cases where regenerative medicine, etc. is to be provided as part of research)
- 6) Anticipated benefits and risks of the regenerative medical care, etc.
- 7) The refusal to receive regenerative medicine, etc. is voluntary.
- 8) Withdrawal of consent.
- 9) The patient shall not be treated disadvantageously by refusing to receive regenerative medicine, etc. or by withdrawing consent.
- 10) The method of disclosing information on the research (limited to cases where regenerative medicine, etc. is conducted as research).
- 11) The fact that research protocols and other materials related to the implementation of the research may be obtained or inspected upon request by the person receiving regenerative medicine, etc. or a surrogate, and the method of obtaining or inspecting such materials (limited to cases where regenerative medicine, etc. is performed as part of the research).
- 12) The protection of personal information of persons receiving regenerative medicine, etc.
- 13) Methods of storage and disposal of samples, etc.
- 14) Status of involvement in research as prescribed in each item of Article 8-8(1) (limited to cases where regenerative medicine, etc. is performed as research)
- 15) System for responding to complaints and inquiries
- 16) The costs involved in the regenerative medicine, etc.
- 17) Existence and details of other treatment methods, and comparison with the expected benefits and risks of other treatments.
- 18) Compensation for damage to health resulting from the provision of the regenerative medicine, etc. (limited to cases where regenerative medicine, etc. is provided as part of research).
- 19) Handling of the important findings (including incidental findings) that may be obtained concerning the health of a subject who receives regenerative medicine, etc., or genetic characteristics that can be passed on to offspring,

etc., if there is a possibility.

- 20) If there is a possibility that a sample, etc. obtained from a subject who receives regenerative medicine, etc., will be used for future research that is not specified at the time consent is obtained from the subject or will be provided to other medical institutions, a statement to that effect and the details of such research that are assumed at the time consent is obtained.
- 21) Matters to be examined by the Specified Authorized Regenerative Medicine Committee, that conducts the examination of the regenerative medicine etc., and other matters related to the Specified Authorized Regenerative Medicine Committee, related to the regenerative medicine, etc.
- 22) In the case where research is conducted with the provision of research funds, etc. by a manufacturer or seller of pharmaceuticals, etc. who manufactures and sells or intends to manufacture and sell pharmaceuticals, etc. to be used in the research or their specifically related entities, the details of the contract prescribed in Article 32 of the Act on the Safety of Regenerative Medicine (limited to the case where regenerative medicine, etc. is conducted as research).
- 23) Other matters necessary for the provision of the regenerative medicine, etc.

